#### Primary outcome measurement.

The West Aphasia Battery (WAB) will be utilized to assess and monitor the improvement and deterioration of aphasia [42]. The assessment involves six language functions, which include spontaneous speech, auditory verbal comprehension, repetition, naming and word finding, reading, and writing. In the evaluation of aphasia, the AQ score is calculated to determine the severity of the condition. A higher AQ score indicates a milder form of aphasia and better language capabilities. The formula for calculating the AQ score is as follows: AQ = 2 × (spontaneous speech + auditory comprehension/20 + repetition/10 + naming/10). The total score is 100 points; higher scores suggest milder aphasia and improved language skills. AQ < 93.8 signifies aphasia.

#### Secondary outcome measurements.

All participants will undergo head MRI scans using a 3.0T, 48-channel MRI scanner (GE Healthcare, USA). T1-weighted sequences, T2-weighted sequences, and T2-fluid attenuated inversion recovery (FLAIR) will be obtained to identify and extract lesions. Resting-state functional MRI (rs-fMRI) will be conducted to evaluate local and global functional connectivity networks associated with language function enhancement. Moreover, diffusion tensor imaging (DTI) and Arterial Spin Labeling (ASL) sequences will be utilized to investigate changes in brain fibers and cerebral blood flow related to cerebellar stimulation on PSA, respectively. During the scanning procedure, rubber earplugs will be used to reduce noise, and foam pads will be utilized to secure the head position and minimize motion artifacts. In the rs-fMRI scanning session, participants will be instructed to close their eyes and remain awake.

In addition, the Loewenstein Occupational Therapy Cognitive Assessment (LOTCA) will be used to measure nonverbal cognitive function, encompassing domains of orientation, visual perception, spatial perception, motor praxis, visuo-motor organization, thinking operations and attention [47–48]. The total score ranges from 26 to 115 (the attention score was computed separately, ranging from 1 to 4). A lower score signifies more severe cognitive deficits.

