**Methods:**

Our study will recruit sixty-six PSA patients, who will be randomly divided into either a real or a sham rTMS group with equal distribution. The real rTMS group (n  =  33) will receive rTMS treatment over the right cerebellar hemisphere along with speech-language therapy (SLT), while the sham group (n  =  33) will receive sham stimulation and SLT. We will assess the outcomes at five intervals: before rTMS treatment, 2, 12, and 24 weeks, and 1-year post-treatment. The primary outcome in this research is the change in performance of the West Aphasia Battery from baseline to the final follow-up. Secondary outcomes include alterations in the structure, function, and perfusion neuroimaging data, as well as changes in non-verbal cognitive functions, measured using the Loewenstein Occupational Therapy Cognitive Assessment over time and between the groups. Any adverse event related to rTMS therapy will also be recorded. The results of this trial will provide insights into whether cerebellar rTMS stimulation (1) improves language function recovery in subacute phase PSA patients; (2) strengthens the functional connection of the cerebro-cerebellar network, and (3) enhances aphasia treatment outcomes by improving non-linguistic cognitive functions. We commenced patient recruitment for this trial in June 2026, and it is currently in progress.

**Registration** This project was prospectively registered at the Chinese Clinical Trial Registry (ChiCTR2600125453).

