The majority of prior research, however, has focused on chronic stroke phase aphasia patients whose functional brain structures have already undergone irreversible alterations [4,33,34]. This could potentially explain the observed lack of significant effects of cerebellar NIBS on language recovery [22,35]. Recent guidelines indicate the safe and tolerable application of NIBS even in the sub-acute phase, with no severe adverse effects reported [36–39]. The current study protocol proposes to stimulate the right cerebellum with repetitive transcranial magnetic stimulation (rTMS) in order to enhance SLT for PSA patients in the sub-acute phase. The study’s primary objective is to assess the short- and long-term efficacy of cerebellar rTMS for aphasia recovery in these patients under a randomized, sham-controlled design. The secondary purpose is to examine alterations in functional connectivity between the cerebellum and language-related cortical regions pre- and post-treatment and elucidate the neural restructuring mechanism. Moreover, from a neuropsychological perspective, the study will investigate whether cerebellar stimulation can improve language symptoms through enhancing non-linguistic cognitive functions.

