### Eligibility criteria

#### Inclusion criteria.

To be eligible for the study, participants must be 18 years or older, right-handed, modern standard Chinese Mandarin-speaking (primary language), with more than 6 years of educational level. The study will collect first-onset stroke aphasia patients with the National Institute of Health stroke scale (NIHSS) score ≤ 3 and the lesion located in the left cerebral hemisphere. Patients will be diagnosed according to current clinical diagnostic criteria of ischemic stroke based on informant report, neurological examination, and brain neuroimaging [41]. And aphasia will be diagnosed by the western aphasia battery (WAB) with the standard of aphasia quotient (AQ)< 93.8 [42]. (See the detailed description about the scale in the primary outcome part)

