#### Exclusion criteria.

Exclusion criteria comprise pre-existing language barrier or aphasia caused by other disorders. History of other neurological diseases (e.g., cerebral small vessel disease, Alzheimer’s disease), mental illnesses (e.g., schizophrenia), other system diseases (e.g., hypothyroidism) which may cause cognitive impairments and consuming diseases or general poor health are further exclusion criteria for all participants. Furthermore, participants who are unable to cooperate in completing the assessment scales and have contraindications for rTMS therapy and MRI examination will not be recruited.

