### Sample size

The sample size was estimated using G*power of 3.1.9.6 (www.gpower.hhu.de) [43–44], with the following parameters: effect size (*d*) = 0.86, α = 0.05 (two tails), power (1–β) = 90%, and allocation ratio n2/n1 = 1. The effect size was determined based on the result of our pilot study. The sample size in the current study should be 60 (30 in each group) after calculation. Considering a 10% dropout rate, a total of 66 patients are aimed to be recruited finally.

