### Outcome measurement

Outcome measures will be assessed across five time points: prior to rTMS treatment (T0), and at 2 weeks (T1), 3 months (T2), 6 months (T3), and 1 year (T4) post-treatment. The primary outcome is the evaluation of language function. Neuroimaging data, along with evaluations of non-linguistic cognitive functions, will serve as secondary outcome measures (Table 1).

**Table 1 pone.0354837.t001:** Outcome measures.

Outcome measures
**Primary outcome measures** ● WAB for determining the presence of aphasia and assessing language dysfunction recovery and deterioration.
**Secondary outcome measures** ● Imaging data for evaluating the structural, function and perfusion alterations in brain area. ● LOTCA for assessing nonverbal cognitive function.
**Safety outcome** ● Incidence of adverse events. ● VAS for assessing headache symptoms. ● FSAS for assessing fatigue symptoms.

Abbreviation: WAB: West Aphasia Battery; LOTCA: The Loewenstein Occupational Therapy Cognitive Assessment; VAS: Visual Analog Scale; FSAS: Fatigue Self-Assessment Scale.

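### The LOTCA total read as non-verbal cognition includes orientation, so in an all-aphasic sample language recovery can raise it; the non-linguistic conclusion needs a supporting score without orientation

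*Protocol article*

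**What the plan says.** Table 1 of the protocol article (Outcome measurement) lists a secondary outcome as "LOTCA for assessing nonverbal cognitive function". The section Secondary outcome measurements says that the instrument "will be used to measure nonverbal cognitive function, encompassing domains of orientation, visual perception, spatial perception, motor praxis, visuo-motor organization, thinking operations and attention". On scoring it says: "The total score ranges from 26 to 115 (the attention score was computed separately, ranging from 1 to 4", and adds that lower scores mean worse cognition. No other composite is described.

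Everyone enrolled has a language deficit, since under Inclusion criteria "aphasia will be diagnosed by the western aphasia battery (WAB) with the standard of aphasia quotient (AQ)< 93.8". Exclusion criteria remove "participants who are unable to cooperate in completing the assessment scales".

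The endpoint carries a stated aim. In the Introduction, "the study will investigate whether cerebellar stimulation can improve language symptoms through enhancing non-linguistic cognitive functions". Aim (3) in the Abstract asks whether stimulation "enhances aphasia treatment outcomes by improving non-linguistic cognitive functions". Expected conclusion (1) in the Discussion predicts better language and better non-verbal cognition in the rTMS group than in the sham group.

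**The concern.** The mechanism aim runs from stimulation to non-linguistic cognition to language. To support it, the cognitive measure must be separable from language. Orientation is a weak point here: it is ordinarily examined by asking questions that the patient must understand and answer, and comprehension and speech are what the WAB measures as the primary outcome.

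If language improves, orientation can improve with it while visual perception, spatial perception, praxis and visuo-motor organization stay where they were. Three readings of the data are exposed:

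- **Between arms.** The trial expects more language gain with real stimulation. Any spill-over into orientation would then favour the real arm. Randomisation and blinding do not remove it, because it arises after allocation, through the treatment's effect on language.
- **Before and after treatment within an arm.** Both arms receive language training, so language gain in either arm can lift the score.
- **Relation with AQ or imaging.** A shared language component creates an association between LOTCA and AQ even if non-verbal cognition never changes.

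In each case, language raising the cognitive score would look like cognition helping language. This belongs to the measure, and no choice of test in the Behavior data analysis section repairs it.

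**Working it through.** **1. What the text fixes.** Seven domains are listed and orientation is the first. Attention alone is scored apart, so orientation lies inside the described total. The span of the total is 115 − 26 = 89 points.

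**2. What the text leaves open.** It gives no points for orientation, no response mode (speech, pointing, multiple choice), no SD of LOTCA change, and no statement that the total rather than the domain scores is analysed. Any size is therefore conditional.

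**3. The trial's own size, used below.** The Sample size section has an effect size of "0.86, α = 0.05 (two tails), power (1–β) = 90%, and allocation ratio n2/n1 = 1". The two-sample t calculation gives 29.41, hence 30 per arm, with power 0.906 at 30. This matches the stated 60, and 60 × 1.1 = 66. The sample size is for the trial as a whole and does not depend on this point.

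**4. Shift in the total from language alone.** Shift = (orientation span) × (extra gain in the real arm, as a fraction of that span).

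Assumption: orientation is two items scored 1 to 8, so its span is 16 − 2 = 14 points, and 14/89 = 15.7% of the total's span.

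- 10%: 14 × 0.10 = 1.4 points
- 25%: 14 × 0.25 = 3.5 points
- 50%: 14 × 0.50 = 7.0 points

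Wider range, with orientation at 10% to 30% of the span: from 89 × 0.10 × 0.10 = 0.9 to 89 × 0.30 × 0.50 = 13.4 points.

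**5. What such a shift does to the between-arm test.** Assume no true non-verbal effect, 30 per arm, two-sided 5%, and an SD of LOTCA change of 8, 12 or 16 points (assumed). The standardised shift is shift/SD, for example 3.5/12 = 0.29. The chance of a significant LOTCA difference is:

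| Shift (points) | SD 8 | SD 12 | SD 16 |
|---|---|---|---|
| 1.4 | 10% | 7% | 6% |
| 3.5 | 39% | 20% | 13% |
| 7.0 | 92% | 60% | 39% |

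The nominal rate is 5%. The bias could be trivial or large, and the document does not allow a choice between the two.

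**The case against.** The strongest reply is that the article never says how orientation is asked or answered. The instrument sources it cites might describe pointing, multiple choice or cueing, and an adapted administration may be in use. Nor does it name the total as the analysed variable. The range may be given only to describe the scale, and the listed domains are compatible with domain-level analysis in a fuller document. Both points stand. A reader might infer that the analysed endpoint is certainly the total, or that recovery of speech certainly raises it. The text supports neither.

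The magnitude is also open to challenge. A reader might infer that one patient could gain most or all of the 14 assumed points through speech alone. That would need near-floor orientation at entry, which is unlikely when NIHSS must be 3 or below and patients who cannot cooperate with the scales are excluded. Such a figure would in any case describe one person's gain and not a difference between arms. A reader might also infer that a LOTCA difference could come entirely from orientation. With orientation at about 16% of the span under the assumption used, that is not shown.

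Finally, removing orientation alone is somewhat arbitrary. Other domains may need spoken answers, thinking operations being the obvious one to check, and the remainder is not a published score. This argues against replacing the total. It does not argue against a supportive score.

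The mismatch survives these replies. The article itself sets out the construct, the domains and the composite, and it draws a conclusion that requires separation from language. The exclusion criterion does not close the gap: those who can be tested still have AQ below 93.8 and room to improve.

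**Conclusion.** The concern holds as a risk to interpretation. The score is labelled non-verbal, its described total contains a domain usually examined through language, the whole sample is aphasic, and one stated aim and one expected conclusion depend on the score being non-linguistic. Language recovery can therefore raise the score without a change in non-verbal cognition, and any such bias would favour the real arm if language improves more there.

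Its size is not known. With orientation at 14 of 89 points and a differential gain of 10% to 50% of its span, the total shifts by about 1.4 to 7 points. The orientation points, the differential gain and the SD of change behind the table are all assumptions. The text does not support going further and calling the LOTCA invalid here, or saying that any observed difference would be spurious.

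The consequence is confined to a secondary endpoint and the mechanism claim.

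**What to change.** Keep the full LOTCA total as reported, and before any unblinded data are seen (recruitment began on June 1, 2026):

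1. State how orientation is administered to and answered by participants with aphasia, and check whether thinking operations or any other domain needs spoken answers.
2. Pre-specify results by domain, and a supportive LOTCA score without orientation and without any other domain found at step 1 to need spoken answers.
3. Require the between-arm difference, and the relation with AQ or imaging, to hold on the reduced score before concluding a gain in non-linguistic cognition under aim (3) or expected conclusion (1). If only the full total moves, report that without the non-linguistic interpretation.

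The cost is a few lines in the outcome and analysis sections. No new data are needed, since the domains are already assessed, and the primary endpoint and sample size do not change. The downside is that the reduced score is a non-standard subset, less comparable with published totals; the full total is still reported for that purpose.

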#### Safety.

The rTMS Adverse Effects Questionnaire will be used to evaluate whether there are any adverse reactions such as burning, headache, tinnitus, anxiety, depression, and seizures in the two groups of patients during and after rTMS treatment. Headache and/or fatigue symptoms will prompt evaluations using the Visual Analog Scale (VAS) and Fatigue Self-Assessment Scale (FSAS) [49–50]. The safety assessments will be conducted after each intervention for all patients.

### Statistical analysis

#### Behavior data analysis.

SPSS 26.0 statistical software will be used to analyze behavior data (the performance of scale assessment which mentioned above). We will use the Intention-to-treat analysis in this study. Shapiro-Wilk test will be used to verify whether the data are normally distributed. For normally distributed measures, t-test and repeated-measures analysis of variances will be used to compare the behavior functions between the same group before and after treatment and between the real and sham rTMS group in the same phase. For non-normally distributed measures, the Mann-Whitney U Test and Kruskal-Wallis H test will be used for comparison across the conditions. P-value < 0.05 is considered significant (two-tailed).

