### Limitations and prospects of the trial

First, this study is constrained by its small sample size and single-center design. Additionally, the year-long follow-up period may lead to unpredictable dropout rates. Furthermore, despite efforts to match age and education levels between the sham and real rTMS groups, individual differences may result in distinct baseline conditions that could influence outcomes. The diverse mechanism of aphasia types poses another challenge, as subgroup analyses based on these types are impeded by the limited sample size. Future research should involve a prospective, multicenter, randomized controlled trial with a larger cohort to validate the current findings. While serving as a preliminary investigation, this study offers valuable insights and potential non-invasive stimulation approaches for enhancing language function in patients with PSA.

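### Intention-to-treat is promised, but the tests named for the scales omit randomised patients with missing visits unless values are imputed first, and no such step is stated

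*Protocol article*

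**What the plan says.** Under Statistical analysis, Behavior data analysis, the article promises the population: "We will use the Intention-to-treat analysis in this study". The same paragraph then fixes the tests. "For normally distributed measures, t-test and repeated-measures analysis of variances will be used to compare the behavior functions", within a group before and after treatment and between groups in the same phase. "For non-normally distributed measures, the Mann-Whitney U Test and Kruskal-Wallis H test will be used for comparison across the conditions". The software is SPSS 26.0.

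The scales are measured at five time points, T0 to T4, the last at one year (Outcome measurement). The Abstract defines the primary outcome as the change in WAB from baseline to the final follow-up.

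Two sections expect losses. Sample size: "Considering a 10% dropout rate, a total of 66 patients are aimed to be recruited finally". Limitations and prospects of the trial: "the year-long follow-up period may lead to unpredictable dropout rates".

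The article mentions no imputation, mixed model or other way of keeping a patient with a missing visit.

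**The concern.** An intention-to-treat analysis compares all randomised patients in the arms to which they were allocated. Each test named here works only on the patients who have the values it needs. If nothing is done about missing values first, the population label and the tests disagree, and the result would be reported as intention-to-treat although some randomised patients are left out.

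Two things are at stake. If patients stop attending for reasons linked to recovery, and the pattern differs between arms, the patients who remain are no longer comparable and the group difference is biased. In addition, the earlier visits of patients who later drop out are not used, although they carry information about the one-year value.

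**Working it through.** **1. Which patients each named test uses (no imputation)**

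| Test | Patient is lost if |
|---|---|
| Repeated-measures ANOVA, usual SPSS procedure | any visit entered in the model is missing |
| t-test or Mann-Whitney U on change to T4 | T0 or T4 is missing |

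The second row is an available-case analysis: missing T1, T2 or T3 costs it nothing. Both rows lose a patient who has left before one year.

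**2. The plan's own sample size**

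Inputs (Sample size section): d = 0.86, two-sided alpha 0.05, power 90%, 1:1. Two-sample t-test with n per arm: noncentrality d × √(n/2), degrees of freedom 2n − 2.

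- n = 30: 0.86 × √15 = 3.33, power 0.906
- n = 29: power 0.896

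So 30 per arm, 60 in total, is reproduced. The recruited total follows as 60 × 1.10 = 66 (60 / 0.90 would give 67). The inflation itself treats dropouts as absent from the analysis.

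**3. Power under loss**

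- At the documented 10%: 66 × 0.90 = 59.4 patients, 29.7 per arm, power 0.90.
- At 20% (assumed): 26.4 per arm, power 0.87.
- At 30% (assumed): 23.1 per arm, power 0.82.

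At the only loss rate in the document, planned power holds.

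**4. Possible bias (illustration; every dropout input is an assumption)**

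Setting: no true effect, 33 per arm, standardised outcome, correlation 0.8 between the earlier visit (T2) and T4. The probability of dropout depends on the T2 value through a logistic curve with slope 2 or 3 per SD. The T4 difference among remaining patients was tested by t-test in 20,000 replicates per setting.

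| Dropout sham / real | Who leaves | Bias (SD) | Two-sided rejection |
|---|---|---|---|
| 15% / 5% | poor recoverers from sham, good from real | 0.22 to 0.26 | 14 to 18% |
| 10% / 10% | poor recoverers from sham, good from real | 0.23 to 0.26 | 14 to 19% |
| 15% / 5% | poor recoverers from both | 0.10 to 0.11 | about 7% |
| 10% / 10% | poor recoverers from both | about 0 | about 5% |

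Upper limits follow from strict truncation. Removing a share p from one tail shifts the T4 mean by 0.8 × φ(z_p)/(1 − p).

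- 15% / 5%, opposite tails: 0.8 × (0.2332/0.85 + 0.1031/0.95) = 0.8 × (0.274 + 0.109) = 0.306 SD
- 10% / 10%, opposite tails: 0.8 × 2 × 0.1755/0.90 = 0.312 SD
- 15% / 5%, same tail: 0.8 × (0.274 − 0.109) = 0.133 SD

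The first two settings are therefore near the worst case. As drawn, the bias in the first three runs against real rTMS, and in the opposite-pattern settings a false finding in favour of rTMS occurred in only 0.1 to 0.2% of replicates. Swapping the arms reverses the sign.

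An estimate that also uses T2 from every randomised patient had bias below 0.01 SD in all four settings. That is expected, because dropout was made to depend on the observed T2; it shows what the earlier visits can recover when that assumption is true.

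**The case against.** The strongest reply is that the article nowhere says that patients with missing visits are excluded. Imputation can precede any of the named tests, and how missing values are handled is commonly left to an analysis plan, which is not shown here. That stands in part: the tests are compatible with intention-to-treat if values are imputed first. What remains is not mere missing detail. The article has fixed both the population and the tests, and run as named, without a further step, the tests do not analyse that population.

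A reader might also infer more than the document supports:

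- **That the whole analysis is complete-case over five visits.** The article does not say which visits enter the ANOVA, and the t-test at T4 loses only patients without T4 or T0.
- **That the trial is underpowered.** If 3 to 8% of patients also missed each of T1 to T3, a five-visit ANOVA would keep about 54 to 46 of 66, and the t-test formula with those numbers gives power 0.87 to 0.82. But those miss rates are not in the document, and a t-test at T4 would not lose those patients.
- **That there is a risk of nearly one in five of falsely declaring rTMS effective.** Rejection of that order needs opposite dropout patterns in the two arms, and in the setting drawn nearly all of it favours sham.

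Finally, a mixed model is not the only acceptable remedy; multiple imputation followed by the named tests would also keep the promise.

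**Conclusion.** The point holds as a mismatch between the promised population and the named tests, in a trial that expects dropout. Unless values are imputed first, the primary one-year comparison omits some randomised patients. At the planned 10% total loss, power stays near 0.90, so the harm lies in possible bias and discarded data.

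Illustratively the bias is about 0.1 to 0.26 SD in either direction when dropout depends on recovery differently in the two arms. Against the design effect of 0.86 that is 0.1/0.86 = 12% to 0.26/0.86 = 30%. It is about zero when dropout has the same rate and pattern in both arms and there is no true effect. These sizes rest on the assumed dropout rates, the assumed link to recovery and the assumed correlation of 0.8; none of these is in the document. It also gives no SD for the AQ, so the bias is left in SD units.

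This should be fixed before analysis, but it does not invalidate the design.

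**What to change.** In Behavior data analysis, for the WAB-AQ:

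- Replace repeated-measures ANOVA and the per-visit t-tests with a mixed model for repeated measures (SPSS MIXED, REML) that includes all randomised patients as randomised and all observed visits. The group contrast in change from baseline to T4 is primary. Entering T0 as one of the response visits keeps a patient who has only a baseline value.
- Alternatively, keep the named tests and state that they follow multiple imputation. If rank tests are retained for any scale, state the missing-data rule for them too.
- Add one sensitivity analysis that shifts the values of dropouts over a stated range.

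The cost is wording and a little more analysis work, in the software already named and with no new patients, visits or data. Recruitment is planned to run to the end of 2028 (Trial status), so the change can be made well before analysis. The downside is that the mixed model relies on data being missing at random, which the sensitivity analysis is there to probe.

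### The primary outcome is change in WAB, but the behavioural analysis names no between-arm test of that change and no baseline adjustment

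*Protocol article*

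**What the plan says.** The Abstract (Methods) states: "The primary outcome in this research is the change in performance of the West Aphasia Battery from baseline to the final follow-up". The Outcome measurement section is looser: "The primary outcome is the evaluation of language function", with neither a change score nor a visit attached. WAB is assessed at five visits, T0 (before treatment) to T4 (one year after treatment), and summarised as the aphasia quotient, AQ.

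Under Behavior data analysis, the parametric methods (t-test and repeated-measures ANOVA, kept for measures that pass the normality check) have this stated purpose: "compare the behavior functions between the same group before and after treatment and between the real and sham rTMS group in the same phase". When normality fails, the text reads: "the Mann-Whitney U Test and Kruskal-Wallis H test will be used for comparison across the conditions".

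The Limitations section accepts that "individual differences may result in distinct baseline conditions that could influence outcomes". The behavioural analysis section contains no term for baseline.

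The Sample size section uses d = 0.86 from a pilot study, two-sided α = 0.05, 90% power and 1:1 allocation. It arrives at 60 patients, raised to 66 for dropout, and does not say whether d is on the change or on the follow-up score.

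**The concern.** The declared endpoint is a change, so the treatment effect is the difference between arms in that change. The section fixes two other comparisons.

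- **Before versus after within an arm.** Both arms receive speech-language therapy in the sub-acute phase, when recovery is expected anyway. Improvement within the real arm mixes any stimulation effect with therapy and natural recovery. Finding significance in one arm and not in the other is not a test of treatment.
- **Real versus sham at one visit.** Read as a comparison of scores at that visit, this carries the full between-patient spread in AQ and takes no account of where each patient started.

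In the non-normal branch the gap is plainer. Mann-Whitney U and Kruskal-Wallis H assume independent groups. They cannot handle before/after pairs, and they test a difference in change only if they are run on change scores, which is not stated.

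At stake are power for the primary question, sensitivity to a chance baseline gap, and freedom to choose the primary contrast after the data are seen.

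**Working it through.** **1. The plan's own figure.** Two-sample t-test, noncentral t, d = 0.86, two-sided 0.05: power is 0.896 at 29 per arm and 0.906 at 30 per arm. So n = 30 per arm, N = 60, and 60 × 1.1 = 66. The stated size reproduces. It is the size for a single two-group t-test, and it fits the declared endpoint only if that test is run on change.

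**2. Power by analysis.** Inputs: 30 per arm and d = 0.86 (Sample size section). Assumed, because the documents do not give them: correlation r between T0 and T4 AQ, and equal SDs at the two visits. The loss of one degree of freedom for the covariate is ignored.

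Case A, d is on change. The SD of change is √(2(1 − r)) times the SD of a single score, so
- raw T4 comparison: d_raw = 0.86 × √(2(1 − r))
- baseline-adjusted: d_adj = d_raw / √(1 − r²)

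Example, r = 0.7: d_raw = 0.86 × √0.6 = 0.666; d_adj = 0.666 / √0.51 = 0.93.

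| r | d_raw | raw T4 | change score | baseline-adjusted |
|---|---|---|---|---|
| 0.3 | 1.018 | 0.972 | 0.906 | 0.982 |
| 0.5 | 0.860 | 0.906 | 0.906 | 0.966 |
| 0.6 | 0.769 | 0.834 | 0.906 | 0.956 |
| 0.7 | 0.666 | 0.718 | 0.906 | 0.944 |
| 0.8 | 0.544 | 0.544 | 0.906 | 0.932 |

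Case B, d is on the T4 score: d_change = 0.86 / √(2(1 − r)) and d_adj = 0.86 / √(1 − r²).

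| r | raw T4 | change score | baseline-adjusted |
|---|---|---|---|
| 0.3 | 0.906 | 0.791 | 0.930 |
| 0.5 | 0.906 | 0.906 | 0.966 |
| 0.7 | 0.906 | 0.988 | 0.996 |

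The adjusted analysis is the strongest in every row. Its residual SD factor √(1 − r²) = √((1 − r)(1 + r)) never exceeds 1 (raw) or √(2(1 − r)) (change).

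**3. Chance baseline gap.** At 30 per arm the SD of the baseline difference is √(2/30) = 0.258 SD. Given a gap b and no treatment effect, the T4 difference has mean r·b and variance (1 − r²) × 2/30, while the unadjusted test rejects beyond about 1.96 × 0.258 = 0.506. For b = 0.5 the conditional type I error is 0.13, 0.20 and 0.25 at r = 0.5, 0.7 and 0.8. For b = 0.26 it is 0.05, 0.04 and 0.03, so an ordinary gap does not inflate it. A gap of 0.5 SD or more is uncommon: 0.5 / 0.258 = 1.94, a two-sided probability of about 5%.

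**4. Within-arm tests.** Suppose both arms improve equally, with an assumed standardised within-arm change of 0.36. A paired t-test at n = 30 then has power 0.479. The chance that only the real arm is significant is 0.479 × 0.521 = 0.25, and that exactly one arm is, 0.50. With assumed changes of 0.2 and 0.5, the real-only chance is 0.15 and 0.19.

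**The case against.** The strongest reply is that the section does name repeated-measures ANOVA. With two arms and T0 among the visits, such a model can produce a group-by-time test, which is a between-arm test of change. A reader might therefore infer that the difference in change is never tested. The documents do not support that: it is not specified, which is a weaker statement. Likewise, a reader might infer that baseline is ignored throughout. T0 enters the before/after comparison, and what is missing is its use in the stated comparison between arms. That this comparison uses raw scores is the natural reading of one visit at a time, but the text does not say so outright.

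Two further points stand. An unadjusted comparison of randomised arms at T4 is unbiased on average, and its overall type I error is correct, so bias is not the charge. The loss of the planned 90% power is also conditional: it needs d to be on change and r above 0.5. At r = 0.5 there is no loss, and below that the raw comparison gains.

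Nor do the documents say that within-arm significance will decide efficacy. The Expected conclusions section frames the result as real against sham.

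The argument that all this belongs in an unseen analysis plan does not succeed. The section is not silent: it fixes which comparisons the tests serve, and those do not match the endpoint in the abstract. Choice of further covariates, by contrast, can be left to such a plan.

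**Conclusion.** The point holds as a mismatch between endpoint and analysis. Change in WAB to one year is primary, yet no between-arm test of that change is specified, no baseline adjustment is stated, and the non-normal tests do not fit paired data.

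The cost ranges from nothing to a fall in power from 91% to 54%, over r = 0.5 to 0.8 with d on change. With d on the T4 score the planned power is kept. What does not depend on the reading of d is that, over the correlations tabulated, baseline adjustment beats both the raw and the change-score comparison and stays at or above 93%. These figures rest on assumed correlations and equal SDs. The mismatch itself rests only on the text.

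**What to change.** In Behavior data analysis, name one primary analysis: the between-arm difference in WAB AQ change from T0 to T4, estimated by ANCOVA on T4 AQ with baseline AQ as covariate. The T4 arm contrast from a mixed model that adjusts for baseline AQ would serve equally; choose one and state it. With baseline AQ in the model, the arm effect on T4 AQ is the same as the arm effect on change.

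Report within-arm before/after changes descriptively only. In the Sample size section, state whether d = 0.86 refers to change or to the follow-up score. Align the Outcome measurement section with the abstract's definition.

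Age and education may be added as covariates but are not needed for this point. The Limitations remark "despite efforts to match age and education levels between the sham and real rTMS groups" is a separate reporting matter.

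The cost is wording only. Baseline AQ is measured at T0 and is needed for eligibility, so no new data are required. The change should be made before any outcome data are analysed.
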